**Methods:**

This is a study protocol for a cluster randomized controlled intervention follow-up study. In phase I of the study, the primary care health centers in the municipality of Bergen, Norway were randomly allocated to intervention or control groups. The intervention was carried out using the motivational interviewing technique and the common risk factor approach. The intervention group received guidance on diet/oral hygiene and the control group received standard care information. Parental knowledge and children at age 3 and 5 years old will be assessed in a prospective phase II follow-up study compared to native Norwegian controls. The primary outcome will be evaluation of change on parental oral health related knowledge and attitudes. The secondary outcome will assess the impact of the intervention on children’s caries -, body mass index- and oral health related quality of life.

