### Aims

The objectives of this project are:

To investigate the efficacy of a culturally adapted behavioral intervention on knowledge, attitudes, and behaviors related to a child’s risk for dental caries and obesity, with special reference to parents of NW immigrant background, with children aged 0–6 months.To assess the effect of the behavioral intervention on children’s caries increment and family quality of life.To generate research-based information about NW immigrants’ oral health issues, healthcare needs, and utilization of health services.To evaluate possible differences and similarities in oral hygiene and feeding practices among parents of different cultural backgrounds (immigrants and native Norwegians).To monitor parents’ attitudes to their children’s oral health in a follow-up study for children aged 3 and 5 years and to measure the children’s quality of life, body mass index (BMI) and caries status.

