## Hypothesis

We hypothesize that compared to ethnic majority parents in Norway, immigrant parents have poor dietary knowledge, deleterious parental feeding habits and caring behaviors which might trigger caries and obesity among their newborn children. Small children of NW immigrant parents receiving common risk dietary interventions and guidance on hygiene/ feeding practices have better health parameters, including fewer carious lesions, standard BMI, and better quality of life than the control group.

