**Fig. 1 Fig1:**
[figure not shown]
Study plan for phase I

**Phase II (follow-up Study)** involves following and comparing behavioral and attitudinal changes towards oral health and oral health-related quality of life among parental groups from different cultural backgrounds (immigrants, previously involved in phase I and native Norwegians), It also includes BMI measurements of children, and caries status in both the test group (immigrant, IM) and the control group (Norwegian, N) over a two-year period. (Fig. 2).

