#### Secondary outcome measures caries increment

(a) Clinical examination of caries lesions in the maxillary anterior teeth when the child is 24 months of age. Examination at 6 months is not possible because at this age no teeth have yet erupted. The comparison will be carried out between and within the control and intervention groups. Therefore, examination (duration ~ 15 min) was carried out when the child was 24 months. (b) Caries increments between the ages of 3- and 5-years will be registered from public dental health clinic records. The outcomes for control (N) and the test (IM) groups will be compared.

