**Body Mass Index (BMI)**

The BMI of the child will be determined by measuring the height (meter) and weight (Kg) when the child is 5 years old. The control (N) and the test (IM) groups will be compared.

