The main strength of this study is that it is a randomized trial, making it possible to evaluate the effectiveness of an intervention program to prevent caries and obesity. The use of cluster randomization allows the identification of the intervention effects when randomization at individual level is not appropriate. Cluster randomization may help to prevent contamination caused by sharing of information between intervention and control participants. Using a culturally adapted health intervention program, focusing on dietary- and oral hygiene practices among NW immigrant families attending primary health care centers might positively impact parental attitudes towards the oral health of their children. In this study, the collaboration between dental public health and primary health care personnel using the CRFA and MI is an innovation which offers opportunities to address key dietary behaviors that may improve general and oral health, particularly among at-risk children.

A possible limitation of this study is that data will be collected by means of a self-reported questionnaire, in which participants might be inclined to give more socially acceptable answers. The diverse backgrounds and different periods of residence in Norway might influence comparisons between groups as well as the acculturation effects. Finally, the two sessions for data collection limit the potential to draw causal inferences about the influence of parental characteristics on their hygiene/feeding practice knowledge and attitudes.

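### BMI, quality of life and caries increment from 3 to 5 years are compared only between all immigrants and native Norwegians, which cannot test the intervention effect promised for them

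*Protocol article*

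**What the plan says.** **What is promised.** The second aim is "To assess the effect of the behavioral intervention on children’s caries increment and family quality of life". The abstract's Methods paragraph says "The secondary outcome will assess the impact of the intervention on children’s caries -, body mass index- and oral health related quality of life". The second hypothesis states that small children of non-western immigrant parents who receive the intervention "have better health parameters, including fewer carious lesions, standard BMI, and better quality of life than the control group". The Discussion (Need for intervention) presents randomisation as the study's main strength, "making it possible to evaluate the effectiveness of an intervention program to prevent caries and obesity".

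**What is specified for the later child outcomes.**
- Caries increment from 3 to 5 years (Secondary outcome measures, part b): "The outcomes for control (N) and the test (IM) groups will be compared".
- BMI at 5 years: "The control (N) and the test (IM) groups will be compared".
- ECOHIS at 3 and 5 years: the same sentence as for BMI.

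**Who the groups are.** The phase II description under Trial Design refers to "caries status in both the test group (immigrant, IM) and the control group (Norwegian, N) over a two-year period". The inclusion criteria define IM in phase I as the eligible immigrant parents, whatever their health centre's allocation. They carry IM into phase II without splitting it by arm and add N as a new group of Norwegian parents.

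**What is compared by randomised arm.** The two primary outcomes (parental knowledge and parental behaviour) and the examination of the upper front teeth at 24 months (caries increment, part a) are compared between the intervention and control groups.

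**The concern.** The word control changes meaning within the article. Under Trial Design and Randomization it means the health centres allocated to standard care. In the definitions of the three later child outcomes it means native Norwegian families, who were never randomised. Test likewise changes from families offered the intervention to all immigrant families, treated and untreated together.

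The hypothesis about treated immigrant children needs treated and untreated immigrant children to be compared. As specified, the later outcomes put both kinds of children on the same side. A difference between IM and N then combines the background gap between the populations with a diluted intervention effect, and the two cannot be separated. Labelled test versus control, such a difference invites reading as a trial result. BMI and quality of life would be left with no specified test of the intervention, although preventing obesity is part of the study's stated purpose.

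**Working it through.** **1. Promise against stated comparison**

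| Child outcome | Intervention effect promised in | Stated comparison |
|---|---|---|
| Caries at 24 months (part a) | Abstract and hypothesis (caries); aim 2 (caries increment) | Randomised arms |
| Caries increment, 3 to 5 years (part b) | Abstract, aim 2, hypothesis | N versus IM |
| BMI at 5 years | Abstract, hypothesis | N versus IM |
| ECOHIS at 3 and 5 years | Abstract, aim 2, hypothesis | N versus IM |

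One of the four assessments has a randomised comparison and three do not.

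**2. What IM versus N estimates**

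Score each outcome so that higher is worse, in SD units. Let D be the gap between untreated immigrants and Norwegians, d the true benefit of the intervention, and f the treated share of IM. Then

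E(IM − N) = (1 − f)·D + f·(D − d) − 0 = D − f·d.

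Inputs: d = 0.25 is the effect size used in the Sample size section. f = 1/2 follows from the 1:1 allocation if the arms are of similar size. D is not given anywhere in the article, so it is assumed over a range.

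| Assumed D | IM − N if d = 0 | IM − N if d = 0.25 | Randomised contrast if d = 0.25 |
|---|---|---|---|
| 0 | 0 | −0.125 | −0.25 |
| 0.25 | 0.25 | 0.125 | −0.25 |
| 0.50 | 0.50 | 0.375 | −0.25 |

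The sign changes at D = f·d = 0.5 × 0.25 = 0.125. Above that, an effective programme shows the test group doing worse than control. If seven centres split 3 v 4 and f is between 3/7 and 4/7, the change comes at 0.107 to 0.143. One observed difference cannot yield both D and d: an IM − N value of 0.125 fits D = 0.25 with d = 0.25, and equally D = 0.125 with d = 0.

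If IM were read as the intervention arm alone (f = 1), the expectation would be D − d. That still contains D and is still not a randomised contrast.

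**3. Precision of the randomised contrast**

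Inputs: 475 participants in 7 centres (Fig. 3 legend) and between-centre SDs s of 0.1 and 0.25 (Sample size). Assumed: residual SD 1, a 3 v 4 split of centres with participants in proportion (n1 = 204, n2 = 271), one child per participant and no loss to follow-up.

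SE = √[1/n1 + 1/n2 + s²(1/3 + 1/4)]

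- s = 0.1: √(0.0086 + 0.0058) = 0.120
- s = 0.25: √(0.0086 + 0.0365) = 0.212

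With an assumed 30% loss (332 children) these become 0.135 and 0.221. For d = 0.25 and no loss, normal-approximation power at two-sided 5% is Φ(0.25/0.120 − 1.96), about 55%, and Φ(0.25/0.212 − 1.96), about 22%. Allowing for the small number of centres would lower both.

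**The case against.** **The IM versus N comparison has a legitimate purpose.** Aim 4 asks how immigrant and native parents differ, aim 5 asks for follow-up at 3 and 5 years, and the first hypothesis is about immigrants and the ethnic majority. The abstract openly describes phase II as a comparison with native Norwegians. All this stands. The comparison should be kept, and the phase II comparison of parental behaviour and attitudes by cultural background needs no change. It does not follow that the same contrast can serve aim 2 or the second hypothesis.

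**The Statistical analysis section may cover the gap.** It provides for t-tests between intervention and control groups and a repeated-measures model, without limiting either to the primary outcomes. But it names none of the three later outcomes. Its repeated-measures comparison is of baseline with follow-up, while BMI is set for age 5 only and ECOHIS for ages 3 and 5. A general sentence does not displace three outcome-specific ones. It does leave ambiguity rather than proof that no comparison by arm was intended. Fig. 2 is not available here and may split IM by arm, although the text that introduces it does not.

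**A stronger reading is tempting.** A reader might infer that no randomised effect is estimated at all, or that caries has no randomised test. The article does not support this: the primary outcomes and caries at 24 months are compared by arm. As no teeth have erupted at 6 months, the 24-month examination is in effect an increment from birth, though in the upper front teeth only. Nor does aim 2 promise an effect on BMI; that promise is in the abstract and the second hypothesis. It would also go too far to say that nothing related to obesity is compared by arm, since the questionnaire behind the primary outcomes includes items on obesity prevention and sugar intake.

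**The illustration rests on assumptions.** This is correct for the size of D, the treated share and the residual SD. The failure to identify d does not depend on their values.

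**Conclusion.** The point holds for three secondary assessments: caries increment from 3 to 5 years, BMI at 5 years and ECOHIS at 3 and 5 years. As written, their only stated comparison pools the randomised arms and sets them against a non-randomised group, so it cannot answer the intervention question asked of them. BMI and quality of life have no stated randomised comparison; caries has one, at 24 months.

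The size of the distortion cannot be taken from the article, because it gives no immigrant–Norwegian gap in SD units. Under the assumptions shown, the sign of the result turns against an effective programme at a gap of about 0.125 SD. The article's own background, which reports more obesity and caries among non-western immigrant children, makes a gap in that direction its working premise, but how far the difference would reflect background is unknown. The primary outcomes are unaffected.

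**What to change.** In part (b) of the caries outcome and in the BMI and quality-of-life definitions:

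1. Make the test of the intervention effect the comparison of intervention-arm with control-arm immigrant families, by the randomised allocation of their health centre, with an analysis that allows for clustering by centre.
2. Keep IM versus N as a separate, descriptive comparison serving aims 4 and 5 and the first hypothesis.
3. Call N the native reference group, reserve control for the randomised control centres, and stop labelling pooled IM as test.
4. State that no IM–N difference will be reported as an effect of the intervention.

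The cost is new wording in three outcome definitions and one further analysis per outcome. The immigrant families of both arms are already to be followed at 3 and 5 years, so no extra families or visits are needed. The drawback is precision: with six or seven centres (the article gives both numbers) the randomised contrast will be wide, with an SE of about 0.12 to 0.21 SD under the assumptions above and more after losses. The report should give the estimate with its confidence interval and should not read a non-significant result as absence of effect.

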**Quality of life of children /families**

The quality of life of children/families will be measured using a validated instrument (ECOHIS), including a child and family component. The responses of parents to the first questionnaire when the child is 3 years, and when the child is 5 years of age will be collected. The control (N) and the test (IM) groups will be compared.

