Food security describes a situation in which there is physical, social, and economic access to safe, nutritious food, in quantities which meet the dietary needs and food preferences required to ensure an active and healthy life [6]. Food insecurity is reported to affect the well-being of children and adults of immigrant families in many Western countries, including the United States and United Kingdom [6, 7]. For most migrants, both the number of calories and the content of the diet change as a result of diverse factors, including language difficulties, lack of acculturation, shortages of previously used products, and culturally related factors associated with food. These factors underlying dietary changes may all contribute to different diseases, including a higher risk of obesity, type 2 diabetes, and cardiovascular disease as well as dental caries. Kumar and co-authors reported a high prevalence of obesity and overweight among immigrants from Pakistan and Turkey [5]. Studies primarily from the United States and United Kingdom have consistently shown that upon arrival, immigrants have lower BMI than their host-country-born counterparts. After longer residence, however, there is a change to higher BMI, overweight and obesity [8]. Compared with ethnic majority children in Denmark, Norway, and Sweden, non-western (NW) immigrant children show overall poorer health outcomes with respect to diabetes, obesity, oral health, mental health, and well-being [9]. A recent review of meta-analyses of data from studies conducted in developed and developing countries revealed that overweight and obese children had significantly more dental caries than children of normal weight [10]. In the sample population, both conditions were found to be associated with low levels of parental income and education [11]. Some immigrant groups who transition from a fiber-rich, whole grain diet to a high-fat diet with lower vegetable intake might be at increased risk of diabetes and cardiovascular disease [5]. A previous report has revealed that specific dietary habits (frequent intake of sugar and sweetened drinks) were considered to be common risk factors for both childhood obesity and caries [12].

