In addition to dietary habits which constitute risk factors common to obesity and dental caries, other habits uniquely associated with heightened caries risk are common among immigrants. In some immigrant communities toothbrushing, oral hygiene routines and preventive dental care are less common and not regarded as important [13, 14]. Many families seek dental care only when a child is in pain or there is visible decay and preserving baby teeth may not be prioritized [15]. A Norwegian cohort study identified the following significant caries risk indicators among children at age 5 years: a mother consuming a diet very high in fat or sugar, a mother with low education and one or both parents of NW immigrant background [16].

Early childhood caries (ECC) is defined as any form of caries (cavitated or non-cavitated) occurring in the primary dentition of children aged 6 years or younger [17]. In children aged between 2.5 and 3.5 years, a combination of different factors constitutes predictors for developing caries, including the mother’s education, immigrant background, and consumption of candy and sugar-containing beverages [18].

In high-income countries there has been a marked decline in the incidence and prevalence of ECC over recent decades, reducing the psychosocial and economic burden of this disease for individuals and for society [19]. However, ECC remains an important health issue in particular population subgroups and in many countries, including Norway, immigrant children are found to be at high risk. Previous studies have revealed that children of NW immigrant backgrounds have higher caries experience than their native counterparts [17, 20–22]. This is attributed to lack of parental knowledge, poor communication due to language barriers and ethnic and cultural differences.

Children with ECC may experience pain when drinking hot or cold liquids, difficulty chewing and biting, poor appetite, weight loss, disturbed sleep, behavioral changes such as irritability and low self-esteem and a decline in academic achievement [23]. Furthermore, a recent study revealed that ECC has a negative effect on the quality of life (QoL) of preschool children and their families [22]. Further research is needed to determine whether and if so, to what extent, the quality of life of immigrant families living in Norway is affected by their children’s EEC.

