#### Phase II

The immigrant parents involved in the intervention study (IM) and a new group of parents of Norwegian background (N) will be recruited from similar public dental health clinics when they visit these centers for their children’s routine oral health examinations at the ages of 3 and 5 years.

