### Data collection and assessment

#### Data collection instrument

Data will be collected in both phase I and phase II, using a questionnaire intended to elicit parental information about caries and obesity risk behaviors as well as behavioral determinants that will be targeted during the intervention.

The ***first*** part of the interview schedule will assess demographics and socioeconomic status. Demographic data include age, gender, and indicators of socioeconomic and migration status: father’s-mother’s education, occupation, and years of residence in Norway. The ***second*** part of the interview schedule will include parental *knowledge related to* breastfeeding, healthy feeding practices, etiology and prevention of obesity, and dental caries, *attitudes* (food habits, tooth cleaning, regular dental visits), eating habits (sugary food/drinks intake, frequency of consumption of sweet beverages) and different oral hygiene practices. The theory of planned behavior (TPB) will be operationalized according to the practices of the immigrant parents. The ***third*** part of the interview schedule will include information about the parents’ own oral hygiene and dietary habits, cultural traditions, perceived oral health and the utilization of general/dental health services. Finally, the Early Childhood Oral Health Impact Scale (ECOHIS) will be used to measure the quality of life of the children and their families. The ECOHIS is a tool used to analyze the impact of oral health issues on the quality of life of families with children aged between 3 and 5 years [32].

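### The non-randomised phase II comparisons of native and immigrant children name no covariates, so they are open to socioeconomic confounding, and they cannot show the effect of the intervention

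*Protocol article*

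**What the plan says.** All places are in the protocol article.

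- **The contrast.** Under Secondary outcome measures, part (b), on caries increment between 3 and 5 years, the text is "The outcomes for control (N) and the test (IM) groups will be compared". The BMI and quality of life paragraphs use the same form: "The control (N) and the test (IM) groups will be compared".
- **How N arises.** Inclusion criteria, Phase II: "a new group of parents of Norwegian background (N) will be recruited from similar public dental health clinics". No matching is described.
- **Who is in IM.** The phase I families, from both intervention and control health centers (Inclusion criteria; Trial Design).
- **Risk factors.** The Background lists among caries risk indicators at age 5 "a mother with low education and one or both parents of NW immigrant background", and among predictors at 2.5 to 3.5 years "the mother’s education, immigrant background, and consumption of candy and sugar-containing beverages". On caries and obesity together it says "both conditions were found to be associated with low levels of parental income and education".
- **What is recorded.** The questionnaire for both phases covers "age, gender, and indicators of socioeconomic and migration status", namely "father’s-mother’s education, occupation, and years of residence in Norway".
- **Methods.** Statistical analysis names chi-square tests, t-tests with eta coefficients, and a repeated-measures GLM. Education appears there only as a factor by which parental knowledge, attitude and habit scores are broken down.
- **Purpose.** The Abstract says the secondary outcomes assess the intervention's impact on caries, BMI and quality of life. The second Aim and the second part of the Hypothesis say much the same.

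**The concern.** Two separate problems sit in the same contrast.

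First, N against IM is an observational comparison. The protocol treats parental education as related to the outcomes and lists it separately from immigrant background. If education also differs between the groups, a crude difference mixes immigrant background with socioeconomic position. A reader could then credit one with the effect of the other.

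Second, the intervention question is put to these outcomes, but the only contrast stated for them does not separate the randomised arms. Whatever N against IM shows, it cannot say whether the intervention worked.

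**Working it through.** **Is there a plan figure to reproduce?** No. The article gives no sample size, effect size or expected difference for N against IM. Its only calculation (Sample size: at least 300 participants, effect no smaller than 0.25) concerns the phase I randomised contrast and has no bearing here.

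**Step 1: the conditions for confounding, against the text.**

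| Condition | Article | Met? |
|---|---|---|
| Groups not formed by randomisation | N newly recruited in phase II | Yes |
| Factor related to outcome | Education named for caries (twice) and for caries with obesity | Yes |
| Factor recorded | Parental education and occupation in the questionnaire | Yes |
| Factor used in N v IM | No covariate named | No |
| Factor differs between groups | Abstract speaks of greater socioeconomic stress among immigrants; no education distribution given | Suggested, not shown |

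The last row limits the conclusion to open to confounding.

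**Step 2: what the bias could look like.** Every input here is an assumption; none comes from the article.

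*Risk ratio.* With p the proportion with low maternal education and RR its effect on caries, the crude IM/N ratio is multiplied by [p_IM(RR − 1) + 1] / [p_N(RR − 1) + 1].

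- p_N = 0.20, p_IM = 0.30, RR = 1.5: 1.15 / 1.10 = 1.05.
- p_N = 0.20, p_IM = 0.50, RR = 3: 2.00 / 1.40 = 1.43.
- p_N = p_IM = 0.30, any RR: 1.00.

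*Mean difference.* Bias = (p_IM − p_N) × education effect in SD.

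- 0.10 × 0.2 = 0.02 SD.
- 0.30 × 0.5 = 0.15 SD.

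*False-positive rate of a two-sided 5% test* when education is the only source of difference, assuming 150 per group. The standard error is √(2/150) = 0.115 SD, and the rate is Φ(b/SE − 1.96) + Φ(−b/SE − 1.96).

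- b = 0.02: 5.3%.
- b = 0.15: 25.5%.
- b = 0: 5%.

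These ranges run from nothing to something that matters. If low education were more common in N, the sign would reverse.

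**Step 3: what pooling the arms does.** Let δ be the intervention effect and π the share of IM in the intervention arm. Then

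mean(IM) − mean(N) = [mean(IM-control) − mean(N)] + πδ.

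Centers were allocated 1:1, so π is about 0.5 if centers contribute similar numbers. About half of δ enters the contrast, added to an unknown gap between untreated immigrant and native children. One number cannot separate the two. Adjusting for education may change the gap term, but it does not isolate δ.

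**The case against.** The strongest reply is that the point rests on silence. The outcome paragraphs say only that the groups are compared. A GLM can carry covariates, and an analysis plan that is not shown may list them. A reader might infer that the protocol prescribes unadjusted t-tests for N against IM. The text does not go that far: its t-test sentence concerns intervention and control groups, and applying it to N is an inference, helped by N being labelled control. What stands against the reply is that the article has a statistical section, names its methods, uses education for other scores, and names no adjustment for a contrast it knows to be non-randomised.

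A second reply is that the crude difference is legitimate. The fourth and fifth Aims are descriptive, and education may lie partly on the path from immigrant background to disease. This is right, and it is why the crude estimate should stay. A reader might also infer that the study sets out to show that culture explains the gap; the Aims do not say so.

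Third, the article recruits N from similar clinics and concedes in the Discussion that diverse backgrounds and length of residence may affect group comparisons. Neither deals with socioeconomic position.

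Part (a) of the caries outcome, the 24-month examination, compares control and intervention groups and is not affected.

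**Conclusion.** The point holds in a limited form. The three N against IM comparisons are non-randomised, name no covariates, and concern outcomes for which the article itself names parental education as a risk factor. They are open to socioeconomic confounding of unknown size and direction. The illustrative ranges above (0.02 to 0.15 SD; a risk ratio inflated 1.05 to 1.43 times; no bias if education is balanced) rest wholly on assumed inputs.

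Three stronger readings are not supported:

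- That the differences *are* confounded. No education distribution by group is given.
- That the bias can be expressed as a share of the 0.25 effect in Sample size. That figure belongs to the phase I intervention contrast and is no yardstick for N against IM.
- That adjusting for education would reveal a hidden intervention benefit. It would not, because IM pools both arms.

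The mismatch between the intervention purpose and the N against IM contrast needs no assumption about education. It follows from the make-up of the groups. Both matters concern secondary outcomes; they should be put right, but they do not touch the primary questionnaire outcomes.

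**What to change.** For caries increment (3 to 5 years), BMI and ECOHIS:

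1. Report the crude IM against N difference with its interval, labelled as descriptive.
2. Beside it, report a regression-adjusted difference with parental education, occupation, parental age, child age and child sex as covariates, and with dental clinic accounted for. State that the two answer different questions. Income is named in the Background but is not among the socioeconomic items the article lists, so some residual confounding should be acknowledged.
3. Fit group as three levels: IM-intervention, IM-control and N.
4. Base any statement about the intervention on IM-intervention against IM-control, with health-center clustering accounted for by a method suited to few clusters (six in Sample size, seven in the CONSORT legend).
5. Reword the outcome paragraphs so that each says which contrast serves the intervention question and which the descriptive one.

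The cost is one extra model per outcome on items the questionnaire already lists. Adjusted intervals may be slightly wider where the groups overlap little on education. No planned analysis is lost.
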